## Abstract

**Background:**

In patients with critical leg ischemia (CLI), the standard operative choice is an in situ bypass to the lower extremity to improve the patients´ prognosis and quality of life. Postoperative complications after surgery occur in 18 % of the patients, prolonging hospitalization and convalescence. The main operative complication is edema. This can be prevented by early mobilization or stimulation of the natural venous pump in the leg.

**Objective:**

To investigate whether compression therapy with foot pump reduces postoperative edema, facilitates wound healing of the operation wounds, promotes healing of ischemic ulcers, and shortens hospitalization, increasing and improving the patient’s subjective quality of life faster.

**Methods:**

The protocol is designed as a randomized, unblinded prospective study with 50 patients in each group. Standard postoperative routines after bypass surgery, including short-stretch bandaging of the operated legs, are compared to supportive stimulation of the venous pump by an impulsive compression foot pump. The postoperative edema of the leg is measured 10 cm below the patella and 8 cm proximal to the medial malleolus. Measurements are performed preoperatively, 1 and 4 days postoperatively and at discharge.

**Results:**

The primary endpoint is reduction of leg edema by at least 50%. The secondary endpoint includes earlier mobilization in the pump group and decreased length of stay in hospital. Quality of life is evaluated through the European Health Related Quality of Life Questionnaire 5 Dimensions (EQ-5D) and Vascular Quality of Life Questionnaire-6 (VascuQol-6) questionnaires. The start of the study is February 1, 2018, and the end of the study is February 1, 2020. First results will be available April 2020.

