## Introduction

Critical leg ischemia (CLI) is a predominant cause of poor wound healing, leg amputation [1], and has a significant, negative impact on quality of life [2]. In patients with CLI, the standard operative choice is an in situ bypass to the lower extremity to improve the patient's prognosis and quality of life. However, postoperative complications after an in situ bypass occur in 18% of patients, prolonging their hospitalization and convalescence. The main postoperative complication is edema. Measured 10 cm below the patella, edema is developed among approximately 6%-8% during the first day, increasing to 8%-10% at the fourth day (nonpublished). Postoperative edema can be prevented by early mobilization which stimulates the natural venous pump in the leg, but mobilization is often difficult in patients with CLI due to wound problems prior to surgery. In addition, CLI is associated with age and limited walking distance and coexists with other manifest diseases, which might also make mobilization difficult. Supportive stimulation of the venous pump by an impulsive compression foot pump may be an effective solution. Patient’s stimulation of the venous plexus in the arch of the foot has shown to reduce leg edema and thrombosis risk in patients undergoing orthopedic surgery on the lower extremities [3-10]. However, in the literature, there is no description of treatment of vascular surgical patients treated with foot pump. Thus, the primary objective of this study is to investigate whether a foot pump is effective in reducing postoperative edema in patients undergoing an in situ bypass.

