### Outcomes

#### End points

The end points are as follows:

Reduction of leg edema by 50%, 10 cm below the patella and 8 cm proximal of the medial malleolus on the operated leg three days post operation in patients treated with impulsive compression in comparison to nontreated.“Wound complications” are defined according to the national Danish vascular registry “karbase”, including infections, hematoma, and lymph excretion over two days. The pump is expected to have influence on the wounds on the thigh/crus and not in the groin. We therefore separate on wound complications in the groin and the other part of the leg.Time to mobilization in pump treated patients (ie, patient can get out of bed and go to the toilet).Length of stay in hospital.

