### Statistical Analysis and Structural Analysis

Through decreasing the postoperative edema by 50 %, we can reduce the wound complication rate for patients from 18% to 12%, given a sigma of 10 and the two-sided test, with an alpha value of 0.05 and beta of 0.80 involving 44 patients in each group. Assuming a dropout rate of 6 patients in each group, the “sample size” will rise to 50 in each group.

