### Statistical methods

Descriptive statistics will be used to report study results. For binary and categorical variables, tests of differences between the intervention and control group will be analyzed by the chi-square test. For continuous variables, initial tests will be performed to check for normality of data by using histograms, Q-Q plots and the Shapiro-Wilk test. Normally and nonnormally distributed variables will be analyzed by *t* test or the Wilcoxon rank sum test, respectively. *P* values <.05 will be considered statistically significant.

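### The primary endpoint is worded as a hoped-for result (edema reduced by at least 50%), while the stated tests can show only that the arms differ

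*Protocol article*

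**What the plan says.** All places are in the protocol article.

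- Abstract, Results: "The primary endpoint is reduction of leg edema by at least 50" percent. No comparator, site or day is given there.
- End points: "Reduction of leg edema by 50%, 10 cm below the patella and 8 cm proximal of the medial malleolus on the operated leg three days" after surgery, "in patients treated with impulsive compression in comparison to nontreated". The words for a minimum are absent here. The comparison is between arms, and two sites are named without one being primary.
- Introduction: the primary objective is "to investigate whether a foot pump is effective in reducing postoperative edema in patients undergoing an in situ bypass".
- Statistical Analysis and Structural Analysis: "Through decreasing the postoperative edema by 50 %, we can reduce the wound complication rate for patients from 18% to 12" percent, "given a sigma of 10 and the two-sided test, with an alpha value of 0.05 and beta of 0.80 involving 44 patients in each group".
- Statistical methods: chi-square test for binary and categorical variables, t test or Wilcoxon rank sum test for continuous ones, and P "values <.05 will be considered statistically significant". No test refers to 50%.
- Abstract (Methods) and the time schedule: leg circumference is measured before surgery, on days 1 and 4 after it and at discharge. The time schedule adds day 42. No measurement is planned for day 3.

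**The concern.** An endpoint should be a variable that is measured and compared. Here it is a result of a given size. The tests in Statistical methods have no difference as their null hypothesis, so rejecting it supports a claim that the pump reduces edema, not that it halves edema. The primary objective matches the tests. The endpoint wording does not.

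What is at stake is the trial's main conclusion. If the observed reduction is clearly above zero but below 50%, the article gives no single answer on whether the primary endpoint was met. The trial is unblinded, so this is better settled in writing before the data are read.

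**Working it through.** **1. The plan's own figure.** Inputs from Statistical Analysis and Structural Analysis: difference 18 − 12 = 6, sigma 10, two-sided alpha 0.05, power 0.80 (printed as beta).

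n per arm = 2 × (1.960 + 0.8416)² × 10² / 6² = 2 × 7.849 × 100 / 36 = 43.6, so 44. Adding 6 dropouts gives 50.

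The figure reproduces. It treats the two wound complication rates as means. It contains no mean or SD of edema and no test against 50%.

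**2. Assumptions for the rest.** The Introduction gives 8%–10% edema at day 4. This is read here as a mean increase in circumference of 8 to 10 points, although the sentence could also be read as an incidence. No SD of edema is given, so a range is shown. Data are taken as normal with a common SD, 44 per arm.

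**3. What the stated test needs.** SE of the difference = SD × √(2/44) = 0.2132 × SD. With 86 degrees of freedom the critical t is 1.988, so P<.05 requires an observed difference of 0.4238 × SD. At control mean 9:

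| SD | Smallest significant difference | As a relative reduction |
|---|---|---|
| 5 | 2.12 | 23.5% |
| 8 | 3.39 | 37.7% |
| 10 | 4.24 | 47.1% |

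Significance is therefore reached below 50% throughout this range. A 35% reduction (3.15 points) at SD 5.6 gives t = 3.15 / (0.2132 × 5.6) = 2.64, P about .01. That is significant, but short of the Abstract's 50%.

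Power of the same test for a true reduction of only 25% (2.25 points), Φ(2.25 / (0.2132 × SD) − 1.96): 94% at SD 3, 75% at SD 4, 56% at SD 5.

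**4. A true 50% reduction under different readings of success.**

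- *P<.05 on the stated test.* Φ(4.5 / (0.2132 × SD) − 1.96) at control mean 9: 99% at SD 5, 94% at SD 6, 75% at SD 8, 56% at SD 10. Misses run from about 1% to 44%.
- *Observed reduction of at least 50%.* The contrast is pump mean − 0.5 × control mean, with SE = SD × √(1.25/44) = 0.1686 × SD. At a true 50% reduction it is centred on zero, so the probability is 0.5 for any SD or n. Simulation (20,000 trials per setting, control mean 8 to 10, SD 2 to 10) gives 49%–51%, and 43%–50% if P<.05 is required as well.
- *95% confidence bound excluding a reduction below 50%.* The same simulation gives about 2.5%–3%.

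**5. If an observed 50% were required,** an 80% chance of meeting it needs a true reduction of 0.5 + 0.8416 × 0.1686 × SD / control mean. That is 57.1% (mean 10, SD 5) to 67.7% (mean 8, SD 10).

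**The case against.** The best defence is that 50% is simply the effect the authors hope for. The only decision criterion in the article is P<.05. The Abstract words its secondary endpoints in the same way, as earlier mobilization and a shorter stay. Only the Abstract sets a minimum. The sample-size paragraph uses the same 50% as an assumption, and the objectives ask only whether edema is reduced. The exact success criterion may also be set out in a full protocol or analysis plan that is not shown.

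Much of this stands, and it limits the point. A reader might infer that the trial has two competing success rules and would fail half the time under its own assumption. The article does not support that, because it nowhere says that the observed reduction must reach 50%. The one-half figure also holds for any roughly symmetric estimate compared with its own true value, so it is not special to this design.

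A reader might also infer that both sites must pass. That would give 1/4 + arcsin(ρ)/(2π) = 25%, 33% and 43% at correlations 0, 0.5 and 0.9, but no such rule is stated.

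Nor is a per-patient responder reading impossible: the Abstract names no comparator, and a chi-square test is available. The End points section makes it unlikely, since it compares treated with nontreated patients and defines no responder.

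What the defence does not remove is the printed wording. A size of result is named as the primary endpoint, and the printed tests cannot establish it.

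**Conclusion.** The point holds as a mismatch between the stated endpoint and the stated analysis. A significant result would show that the arms differ, not that edema fell by at least 50%. Reductions of roughly 24% to 47% could be significant while short of the endpoint as worded (control mean 9, SD 5 to 10, 44 per arm). The mismatch follows from the text alone. These percentages rest on an assumed edema mean and SD.

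The one-half chance of success is conditional on reading the Abstract literally as a pass mark for the observed reduction, and should not be reported as a property of this trial. Under the P<.05 criterion the article does state, a true 50% effect would be missed in about 1% to 44% of trials on the same assumptions.

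**What to change.** Define the primary endpoint as the between-arm difference in percent change of leg circumference from the preoperative value, at one named site and one named day, tested against no difference at two-sided alpha 0.05. In naming the day, reconcile the three days after surgery in End points with the day 4 measurement in the Abstract and the time schedule. In naming the site, state which of the two is primary.

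Report the relative reduction in mean edema with its 95% confidence interval, so that readers can judge how the result compares with 50%. Present 50% only as the hoped-for effect, not as the endpoint or a pass mark. Add that the 44 per group come from a difference of 6 and a sigma of 10, without any mean or SD of edema, so the sample size was not derived from a 50% edema effect.

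Cost: wording in the Abstract (Results), End points and Statistical methods, plus the note on the sample-size calculation. Data collection does not change.

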**Conclusions:**

In orthopedic surgery of the lower extremities, the use of foot pumps has shown a reduction of edema and thrombosis in risk patients. Although important positive effects may be expected after vein bypass surgery, no reports have yet investigated the use of the device in vascular-operated patients and no analysis or meta Cochrane reviews are available in this field.

**Trial Registration:**

ClinicalTrials.gov NCT03192982; https://clinicaltrials.gov/ct2/show/NCT03192982 (Archived by WebCite at http://www.webcitation.org/6xMZJ06dw)

## Introduction

Critical leg ischemia (CLI) is a predominant cause of poor wound healing, leg amputation [1], and has a significant, negative impact on quality of life [2]. In patients with CLI, the standard operative choice is an in situ bypass to the lower extremity to improve the patient's prognosis and quality of life. However, postoperative complications after an in situ bypass occur in 18% of patients, prolonging their hospitalization and convalescence. The main postoperative complication is edema. Measured 10 cm below the patella, edema is developed among approximately 6%-8% during the first day, increasing to 8%-10% at the fourth day (nonpublished). Postoperative edema can be prevented by early mobilization which stimulates the natural venous pump in the leg, but mobilization is often difficult in patients with CLI due to wound problems prior to surgery. In addition, CLI is associated with age and limited walking distance and coexists with other manifest diseases, which might also make mobilization difficult. Supportive stimulation of the venous pump by an impulsive compression foot pump may be an effective solution. Patient’s stimulation of the venous plexus in the arch of the foot has shown to reduce leg edema and thrombosis risk in patients undergoing orthopedic surgery on the lower extremities [3-10]. However, in the literature, there is no description of treatment of vascular surgical patients treated with foot pump. Thus, the primary objective of this study is to investigate whether a foot pump is effective in reducing postoperative edema in patients undergoing an in situ bypass.

### Background and Rationale

In situ bypass to the lower extremity is the standard operation choice on patients with critical leg ischemia, accounting for approximately 18% of patients’ wound problems [11], prolonging their hospitalization time and convalescence. One of the reasons for wound problems is postoperative edemaThe edema is expected after open vascular reconstruction (in situ bypass surgery). Early mobilization can prevent development of the postoperative edema. Through mobilization, the patient stimulates the natural venous pump in the leg. However, patients are often hard to mobilize in an early stage due to the wound and age. Stimulation of the venous plexus in the arch of the foot has, in other categories of patients, shown to reduce postoperative edema of leg and thrombosis risk in patients undergoing orthopedic surgery on the lower extremities. The subjective quality of life is often impaired in relation to the above mentioned surgical treatment. Through a quicker recovery, the patient can rapidly regain mobility and walking capability.

There is no analysis or meta Cochrane reviews in this field.

### Objectives

The objectives will be as follows:

To investigate whether compression therapy with foot pump reduces postoperative edema.Through reducing edema, facilitate wound healing of the operation wounds, promote healing of ischemic ulcers, and decrease major amputation rate.Shorten hospitalization.Increase and improve the patient’s subjective quality of life faster.

## Methods

The trial design is a 1:1 randomized prospective study. All surgical procedures will be performed by vascular surgeons. The postoperative care will be performed by special nurses in cooperation with vascular surgeons at the Department of Vascular Surgery, Lillebaelt Hospital, Denmark.

### Participants, Interventions, and Outcomes

#### Eligibility criteria

##### Inclusion:

The study will include patients who have undergone in situ from common femoral artery to a popliteal artery above knee/below knee or crural artery.

##### Exclusion:

The study will exclude patients with former deep vein thrombosis, symptomatic postthrombotic syndrome, or ischemic wounds that are in such manner that compression of the foot is not possible.

##### Age of Subjects:

Subjects will be between the ages of 18 and 99 years.

### Interventions

Post operation, the foot pump will be placed on the foot, according to randomization. The pump must be placed on the foot immediately after the operation is finished. The foot pump will be left on the foot until full mobilization is reached. The pump should not harm or hurt the patient when it is placed on the foot in the correct position.

The control group will follow the department’s ordinary postoperative routines for inset bypass short-stretch bandaging. The short-stretch bandage is a padded bandage that stretches from the toes and up to the upper thigh with a 40 mmHg pressure.

### Outcomes

#### End points

The end points are as follows:

Reduction of leg edema by 50%, 10 cm below the patella and 8 cm proximal of the medial malleolus on the operated leg three days post operation in patients treated with impulsive compression in comparison to nontreated.“Wound complications” are defined according to the national Danish vascular registry “karbase”, including infections, hematoma, and lymph excretion over two days. The pump is expected to have influence on the wounds on the thigh/crus and not in the groin. We therefore separate on wound complications in the groin and the other part of the leg.Time to mobilization in pump treated patients (ie, patient can get out of bed and go to the toilet).Length of stay in hospital.

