#### Time Schedule for Measuring Assessing Symptoms As Edema

The time schedule will be as follows:

In the open clinic when the patient is included.The day after the operation.Day 4 and the day of patient discharge.Day 42 (control in our open clinic for control of the operation results).

The measure procedure will be as follows:

The circumference of the leg will be measured at 10 cm below the distal part of the patellae and 8 cm above medial malleolus.In the same procedure, we will evaluate pain by the Visual Analogue Scale (VAS).Randomization when the patient is on the operation table.Operation performed.Post operation.The control group follows the department’s ordinary postoperative routines for inset bypass — short-stretch bandage. A short-stretch bandage is a padded bandage that stretches from the toes and up to the upper thigh with a 40 mmHg pressure.Time for full mobilization is recorded in all patients.Reoperations is noted.Toe pressure is measured at inclusion, immediately post operation and at discharge.Time for discharge is noted.Paraclinical factors to be examined: confusion, pneumonia, infection of the urinary tract.Duplex study at Day 42 of reverse flow in the deep veins associated with standard duplex study of AV fistulas postoperatively.Quality of life questionnaire (VascuQol-6) baseline + 42 days + 6-month + 12-month, (Appendix 1).EQ-5D baseline + 42 days + 6-month + 12-month, (Appendix 2).

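### The primary edema endpoint is set at three days after operation, but the schedule fixes no measurement on that day; the role of the two leg sites should be settled in the same edit

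*Protocol article*

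**What the plan says.** The Results paragraph of the abstract ranks the endpoint: "The primary endpoint is reduction of leg edema by at least 50" per cent. It gives no day and no site. Both come from the End points section, which lists the edema item first but does not itself call any item primary: "Reduction of leg edema by 50%, 10 cm below the patella and 8 cm proximal of the medial malleolus", compared "on the operated leg three days post operation in patients treated with impulsive compression in comparison to nontreated".

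The measurement times appear twice. The abstract's Methods paragraph says: "Measurements are performed preoperatively, 1 and 4 days postoperatively and at discharge". The section headed Time Schedule for Measuring Assessing Symptoms As Edema lists the inclusion visit, the day after surgery, "Day 4 and the day of patient discharge", and a day-42 clinic control. On the procedure it says: "The circumference of the leg will be measured at 10 cm below the distal part of the patellae and 8 cm above medial malleolus".

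The only prior edema figures are in the Introduction. They are for the patella site, at 6%-8% on the first day, "increasing to 8%-10% at the fourth day". The Statistical methods section sets a significance level of P<.05 and does not say how the two sites are to be combined.

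**The concern.** The endpoint is tied to one day and the measurements to others. If the protocol is followed exactly, no visit is designed to produce the primary value, so somebody has to decide which scheduled time stands in for day 3. The trial is unblinded once the pump or bandage is applied. A day left open can then be chosen, knowingly or not, with the results in view.

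The candidates are also not equivalent. By the protocol's own background figures edema is still rising between day 1 and day 4, so day 1 answers a different question. Discharge falls on a different day for each patient, and length of stay is a listed endpoint that the pump is expected to shorten. A comparison at discharge could therefore set pump patients measured earlier against controls measured later.

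The two sites add a second, smaller opening. The endpoint joins them with the word and, but does not say whether that is a decision rule or just a list of where the tape goes.

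**Working it through.** **1. Time point against schedule**

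| Place in the protocol article | Times given for edema or circumference |
|---|---|
| Abstract, Results | none (endpoint labelled primary) |
| End points | three days after operation |
| Abstract, Methods | before operation, 1 day, 4 days, discharge |
| Time schedule | inclusion, day after operation, Day 4, discharge, Day 42 |
| Introduction (prior data, patella site) | first day, fourth day |

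Day 3 occurs once, in the endpoint definition, and nowhere in the schedule.

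**2. Can Day 4 be three days after operation?** Only if the day of operation is counted as Day 1. The time schedule does not define its day zero, so that section alone does not exclude it. The abstract, however, gives the two early visits as 1 and 4 days postoperatively, and the time schedule describes the first of them as the day after operation. If one day postoperatively is the day after surgery, four days postoperatively is the fourth day after surgery. Under the other convention the abstract would have had to read 1 and 3 days. The explanation is unlikely, though not strictly excluded.

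**3. Is any power stated for circumference?** The sample size paragraph gives alpha 0.05 two-sided, sigma 10, 0.80 (written as beta, read here as power) and a fall in wound complications from 18% to 12%. Treated as a difference of 6 with SD 10:

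n = 2 × (1.960 + 0.842)² × 10² / 6² = 2 × 7.85 × 100 / 36 = 43.6, so 44 per group.

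This reproduces the protocol's 44, and 44 + 6 dropouts gives 50. It is one comparison, with its effect expressed as wound complications. The protocol gives no circumference difference or SD at either site, hence no stated power for this endpoint.

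**4. Two sites: illustration only.** The between-site correlation ρ is not in the protocol and is assumed. With no true effect at either site and each tested at two-sided 0.05:

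- Either site suffices, independent sites: 1 − (1 − 0.05)² = 0.0975.
- Either site suffices, correlated sites: 1 − P(|Z1| < 1.96 and |Z2| < 1.96), with bivariate normal Z.
- Both sites required: 0.05 + 0.05 − P(either).

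| Assumed ρ | Either site | Both sites |
|---|---|---|
| 0 | 9.75% | 0.25% |
| 0.3 | 9.51% | 0.49% |
| 0.5 | 9.07% | 0.93% |
| 0.7 | 8.35% | 1.65% |
| 0.9 | 7.04% | 2.96% |

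If there is a true effect at one site only, requiring both still holds the error at or below 5%, because the other site must pass its own 5% test.

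**The case against.** The strongest reply on timing is that Day 4 may simply be the third day after surgery. The time schedule leaves room for this, but the abstract's count speaks against it and no section supports it. It is also fair that discharge is a scheduled measurement, so a patient who goes home on day 3 would have a value then. A reader might infer that the endpoint cannot be observed in anyone; that goes too far. What stands is that no visit is fixed at day 3, and a chance coincidence with discharge does not supply one.

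A further reply is that a statistical analysis plan, not shown here, may settle the day and the site rule. For the site rule this has force: combining two sites is commonly left to that plan. For the day it has less, because any choice must depart from either the endpoint definition or the schedule. The contradiction lies in the protocol's own text.

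On the sites, the plain reading of and is that both must show the reduction, which keeps the error at or below 5%. A reader might infer that the trial's type I error is inflated to nearly 10%. The document does not support this, since it nowhere says that one site is enough. Nor can one infer that the second site erodes the stated 80% power: that figure belongs to a calculation on wound complications, and none is stated for circumference.

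**Conclusion.** The time point is wrong as written. The endpoint labelled primary in the abstract is defined at three days after operation, and the protocol schedules no fixed measurement then. This rests only on setting its sections side by side; the remaining doubt is the undefined day zero in the time schedule, which the abstract's count makes a weak defense. It matters because it leaves the primary data point of an unblinded trial open, with one candidate time that the treatment may itself shift.

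The site question is secondary. The rule is unstated, and the error rate depends on it: about 9.75% to 7.0% if either site suffices (correlation assumed 0 to 0.9), at most 5% if both are required. These figures show why the rule should be written down. They do not show that the error is inflated, and no loss of stated power is claimed.

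**What to change.** In the End points section, change the time to four days after operation. This agrees with the abstract, the time schedule and the later of the two prior figures in the Introduction. Make the day-1, discharge and day-42 circumferences secondary.

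In the same edit, state what the two sites do. Either name the circumference 10 cm below the patella as the single primary measure, with the ankle site secondary, or say that both sites must succeed. The patella site is the natural single choice because it is the only one with prior data quoted, at day 1 as well as day 4. Those data support the site; the choice of day 4 rests on the schedule.

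The cost is wording only, as the day-4 measurement at both sites is already scheduled. The one downside is that the ankle site may lose primary status. The change should be dated and made before outcome data by arm are examined.

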#### Sequence generation

The study will use an online randomization program. The total distribution between the two groups is 1:1, but a block randomizing will be used in different sizes.

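### The planned fall in wound complications from 18% to 12% is stated for all sites together, while the endpoint section expects the pump to act only outside the groin

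*Protocol article*

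**What the plan says.** The End points section of the protocol article takes its definition of wound complications from the Danish vascular registry and then divides them by site. Its reason is explicit: "The pump is expected to have influence on the wounds on the thigh/crus and not in the groin". Groin complications and complications on the other part of the leg are accordingly kept apart.

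The section Statistical Analysis and Structural Analysis makes no such division. It says that by halving the edema "we can reduce the wound complication rate for patients from 18% to 12" (per cent), "given a sigma of 10 and the two-sided test", "with an alpha value of 0.05 and beta of 0.80 involving 44 patients in each group". Six patients per group are then added for dropout, which gives 50.

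The 18% appears in two other forms, neither limited by site:
- Background and Rationale: "accounting for approximately 18% of patients’ wound problems". The wording is unclear, but it refers to wound problems.
- Introduction: "postoperative complications after an in situ bypass occur in 18% of patients". The Abstract says much the same. Here the figure covers postoperative complications of every kind.

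Under Eligibility criteria, the bypass starts at the common femoral artery, so a groin wound belongs to the operation under study.

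**The concern.** The endpoint section and the sample-size paragraph appear to count different events. A groin infection or groin lymph leak falls outside the outcome that the pump is expected to change. Nothing in the sample-size paragraph excludes it from the 18%.

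Two things are at stake. First, the planned effect on wounds may be more ambitious than it looks, because the whole 6-point fall would have to come from the leg wounds alone. Second, wound healing is a declared objective of the trial. If the wound conclusion could rest on the any-site rate or on the leg rate, the result would depend on which one is read. In an any-site comparison, groin events that are not expected to respond weaken the relative effect.

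**Working it through.** **Inputs from the protocol article.** Rates 18% and 12%, sigma 10 (no unit), two-sided alpha 0.05, and 44 per group before dropout, all from Statistical Analysis and Structural Analysis. The stated beta of 0.80 is read as power 0.80. Allocation is 1:1 (Sequence generation). The chi-square test for binary outcomes comes from Statistical methods.

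**Input not in the document.** The share *s* of the 18% that lies outside the groin. It is varied below. Each patient with a complication is counted at one site only, and the groin rate is taken as unchanged by the pump.

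**1. The plan's own figure.** Treating 18 and 12 as means with SD 10:

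n = 2 × (1.960 + 0.842)² × 10² / 6² = 2 × 7.849 × 100 / 36 = 43.6, rounded up to 44 per group. Adding 6 gives 50.

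So 44 reproduces, but only as a comparison of two means. As a comparison of two proportions, with average rate 0.15:

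n = [1.960 × √(2 × 0.15 × 0.85) + 0.842 × √(0.18 × 0.82 + 0.12 × 0.88)]² / 0.06² = 554.8, rounded up to 555 per group.

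Exact enumeration of the uncorrected chi-square test for 18% versus 12% at 44 per arm gives power of 12.9%. The usual normal approximation gives 12.0%. This is the baseline before any split by site.

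**2. What 12% overall asks of the leg wounds.** The leg rate is 0.18*s*. If the groin does not respond, all 6 points come from the leg, so the required relative cut is 0.06 / (0.18*s*).

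| Leg share *s* (assumed) | Leg rate, control to pump | Relative cut needed | Exact power, leg outcome, 44 per arm |
|---|---|---|---|
| 1 | 18% to 12% | 33% | 12.9% |
| 0.75 | 13.5% to 7.5% | 44% | 16% |
| 0.50 | 9% to 3% | 67% | 23% |
| 1/3 | 6% to 0% | 100% | 27% |

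Below *s* = 1/3 the leg rate is under 6%, and 12% overall cannot be reached through leg wounds alone. A patient with complications at both sites remains an any-site event even if the leg wound is prevented, so such patients do not ease the requirement.

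**3. Alternative: keep the one-third cut, but only for leg wounds.** This is an assumption; the plan states no relative reduction. The overall rate then falls to 0.18(1 − *s*) + 0.12*s*.

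| *s* | Any site | Exact power | Leg only | Exact power |
|---|---|---|---|---|
| 0.75 | 18% vs 13.5% | 9.4% | 13.5% vs 9% | 11.2% |
| 0.50 | 18% vs 15% | 7.1% | 9% vs 6% | 9.4% |
| 1/3 | 18% vs 16% | 6.1% | 6% vs 4% | 6.8% |

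At *s* = 0.50 the absolute difference is 3 points on either outcome, half the planned 6. The relative reduction is one third for the leg (3/9) but only one sixth for any site (3/18). That is the dilution.

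**The case against.** The strongest reply is that the two sections can both be true. A fall from 18% to 12% overall is compatible with a pump that acts only outside the groin, provided the leg rate is at least 6%. The document gives no groin share, and if none of the 18% arises in the groin the problem disappears. The source cited for the 18% is not at hand, so whether it counts groin wounds is inferred from the absence of any restriction. All of this stands, and it limits the point to a mismatch of unknown size.

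A reader might also infer that splitting by site is what ruins the power. The figures do not support that. Undivided 18% versus 12% has only about 13% power at 44 per arm before any dilution. If the full 6 points fall on the leg, separating the sites raises power, for example to 23% for 9% versus 3%. The 6% to 11% figures appear only under the one-third relative cut, which the plan does not state.

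A reader might further infer that testing both sites at .05 inflates false positives, to 1 − 0.95² = 9.75% for two independent tests. This is secondary. The endpoint section already indicates which site should respond, so a groin result would not support the stated mechanism. The Abstract names edema as primary and does not list wounds among its secondary endpoints, and multiplicity among such outcomes is commonly left to an analysis plan.

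What survives is that the article itself states both a site-specific expectation and a site-free planning effect. That is not a detail left to another document.

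**Conclusion.** The point holds as a mismatch between planning effect and endpoint. The direction does not depend on the assumed share: if any part of the 18% lies in the groin, the leg rate available to change is below 18%, and reaching 12% overall needs a cut in leg wounds above one third. The size does depend on it: 44% at a leg share of 75%, 67% at 50%, 100% at one third. These figures rest on one site per patient and no pump effect in the groin.

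The documents do not support calling 18% to 12% impossible, or blaming the site split for the low power. The larger weakness in the same sentence is that 44 per group comes from a means formula with difference 6 and SD 10. Correcting that formula alone would leave the mismatch, because the rates would still describe an outcome that the pump is expected to affect only in part. Since edema is the primary endpoint, this is a correction worth making to the wound objective and the sample-size rationale; it does not threaten the primary comparison.

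**What to change.** In End points, name wound complications of the thigh and crus (non-groin) as the single outcome on which the wound conclusion rests. Report groin complications separately and descriptively, as a site where no pump effect is expected, and do not pool the two for the efficacy claim.

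In Statistical Analysis and Structural Analysis, give the expected control and pump rates for that non-groin outcome. The registry already used for the definition is one place to look, if it reports rates by site; the article does not say that it does. If only the 18% is available and it covers all sites, label it so and state what reduction in leg wounds the 12% implies. Do not present 44 per group as giving 80% power for the wound rate.

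The cost is wording in two paragraphs and, if available, a look-up of site-specific rates. The sites are already to be separated, so no new outcome is added, and no extra patients are requested. The downside is real: the named outcome has fewer events (at an assumed 50% leg share, about 0.09 × 44 = 4 control-arm events instead of 0.18 × 44 = 8), and the stated effect and power for wounds will look less favourable.
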